**ABSTRACT**

Cross Training is a high-intensity exercise modality, in which the most demanding part of training and competition is called the WOD (workout of the day). Competitions consist of multiple WODs performed in sequence and across consecutive days, which may lead to muscle fatigue and increase athletes’ susceptibility to injuries. In some sports, therapeutic devices have been used to accelerate muscle recovery or modulate the damage caused by strenuous exercise, such as photobiomodulation therapy combined with a static magnetic field (PBMT-sMF), extracorporeal shock wave therapy (ESWT), and intermittent pneumatic compression (IPC). However, it is still unclear which modality is most effective in promoting faster and more efficient muscle recovery in Cross Training athletes. Therefore, the aim of this study is to compare the isolated and combined effects of three different therapeutic modalities—PBMT-sMF, ESWT, and IPC—on muscle recovery in Cross Training athletes, as well as to investigate whether there will be adverse effects related to physiological recovery. To this end, a randomized, controlled, crossover, blinded clinical trial will be conducted. Male Cross Training athletes aged 18 to 36 years will voluntarily participate and will be randomly allocated to receive, in crossover order, the four interventions (control/passive recovery, PBMT-sMF, ESWT, and IPC) across four weeks of procedures. Muscle recovery will be assessed at baseline (prior to any intervention) and at 1 h, 24 h, and 48 h following a WOD designed to induce fatigue. Assessments will include the primary outcome: performance in a functional test; and secondary outcomes: subjective perception of effort/fatigue measured by the CR-100 scale, physiological variables through analysis of muscle damage via lactate dehydrogenase (LDH) levels, as well as thiobarbituric acid reactive substances (TBARS), carbonylated proteins, catalase (CAT), and superoxide dismutase (SOD) activity to assess oxidative stress. Data will be analyzed both in absolute values and as percentage changes from baseline (pre-exercise) values. The Kolmogorov-Smirnov test will be used to verify data normality. Statistical significance will be set at p < 0.05.

**Keywords:** Photobiomodulation Therapy, Shock Wave Therapy, Intermittent Pneumatic Compression, Fatigue, Performance, Recovery.

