**Study Sessions and Exercise Protocol**

The trial will comprise four sessions with seven-day washouts. Procedures will remain identical except for the randomized intervention applied. Assessments will occur before and after each WOD.

- Exercise Protocol – WOD: To minimize circadian and external influences, participants will perform the WOD at the same time in all sessions and will avoid physical activity from 24 h pre-WOD to 48 h post-WOD. The WOD will follow the Cross Training 21-15-9 scheme (three rounds, no rest), aiming for the fastest possible completion. Repetitions will be monitored by an independent assessor.

The exercises will include:

1. Assault AirBike Calories: Participants will use a standardized AirBike model, pedaling until they reach the target calorie count required for each round.
2. Hang Squat Clean: The exercise will start with the participant holding the barbell in the hang position (above the knees) with arms fully extended. From this position, the barbell will be cleaned to the shoulders while the hips descend below the knees. A repetition will be validated when full hip and knee extension is achieved with the bar resting on the shoulders.
3. Box Jump Over: Participants will perform a two-foot jump onto a 60.69-cm (24-inch) box, ensuring both feet contact the top surface before jumping down to the opposite side.

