**Outcomes**

The primary outcome will be the change in performance on the functional test, assessed 1-hour post-WOD. Secondary outcomes will include: change in functional test performance at 24 and 48 hours post-WOD; biochemical markers of muscle damage and oxidative stress; antioxidant activity; subjective perception of exertion (assessed at 1, 24, and 48 hours post-WOD); and satisfaction with the intervention (assessed at 48 hours post-WOD).

- Vertical Jump Performance: Vertical jump performance will be measured using the countermovement jump (CMJ) height test (Balsalobre-Fernández et al., 2015). During the test, participants will stand with feet shoulder-width apart and hands on the hips. They will perform a controlled squat to ~90° of knee flexion followed by an explosive vertical jump. Upon landing, they will flex the hips, knees, and ankles to absorb impact. A smartphone camera, positioned 1.5 m away, will record three maximal-effort CMJ attempts (Balsalobre-Fernández et al., 2015). Jump height will be analyzed using the JumPo 2 app (iOS), the only validated tool available at the time. The highest recorded jump will be used for analysis.
- Muscle Damage and Oxidative Stress Markers: Muscle damage will be assessed via lactate dehydrogenase (LDH) levels (De Oliveira et al., 2017). Oxidative stress and antioxidant activity will be assessed using thiobarbituric acid reactive substances (TBARS), carbonylated proteins, catalase (CAT), and superoxide dismutase (SOD) (Pinto et al., 2022). Blood samples (5 mL) will be drawn from the anterior cubital vein and stored at −80 °C for later analysis. LDH activity will be quantified by spectrophotometry using specific reagent kits (Labtest®, Minas Gerais, Brazil) as an indirect marker of muscle damage. TBARS, carbonylated proteins, CAT, and SOD will be analyzed as biomarkers of oxidative stress and antioxidant defense following previously established spectrophotometric protocols (Pinto et al., 2022). Each biochemical analysis will be conducted in triplicate, and the mean value will be used for statistical interpretation.
- Subjective Perception of Exertion: Perceived exertion will be assessed using the Rate of Perceived Exertion (RPE) scale (Fanchini et al., Weston et al., 2015). Participants will rate effort in two domains:
- RPE-MI (Muscular Intensity): perceived lower-limb fatigue.
- RPE-R (Respiratory Effort): perceived cardiorespiratory fatigue.

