  Volunteers will complete two identical RPE scales ranging from 0 to 100, corresponding to muscular and cardiorespiratory effort.
- Satisfaction with the Intervention: Satisfaction will be assessed 48 hours post-WOD using a 5-point Likert scale: (1) Very unsatisfied, (2) Unsatisfied, (3) Neutral, (4) Satisfied, (5) Very satisfied. For analysis, responses will be dichotomized as satisfied (“satisfied” and “very satisfied”) versus not satisfied (“neutral,” “unsatisfied,” and “very unsatisfied”).

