**Statistical Analysis**

To the best of our knowledge, no prior study will have compared PBMT-sMF, IPC, ESWT, and passive recovery in Cross Training athletes. Therefore, sample size will be calculated based on CMJ performance data from the first session, following a previously described method (Pinto et al., 2022). This calculation will be conducted by a blinded researcher and will use percentage changes in CMJ at 1-hour post-WOD (primary outcome). An 80% statistical power (α = 0.05; ANOVA) will be considered, and the WebPower (https://webpower.psychstat.org/models/means03/effectsize.php) and Statistics Kingdom (https://www.statskingdom.com/sample_size_regression.html) tools will be used for the computation.

Statistical analyses will follow the intention-to-treat principle (Elkins, 2015). The statistician will remain blinded to allocation to minimize bias. Data normality will be assessed using the Shapiro–Wilk test. Differences between interventions will be evaluated using repeated-measures ANOVA with Bonferroni post hoc tests. Both absolute values and percentage changes from baseline will be analyzed. Results will be presented as mean ± SD (tables) and mean ± SEM (figures). Fisher’s exact test will be used to compare satisfaction proportions across interventions. Statistical significance will be set at p < 0.05.

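### Percentage change from the pre-exercise baseline is planned with no exemption for the 0–100 exertion ratings, where it is undefined at a zero baseline and unstable at a low one

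*Protocol*

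**What the plan says.** The protocol states the analysis scale twice. The Abstract has "Data will be analyzed both in absolute values and as percentage changes from baseline (pre-exercise) values", and the Statistical Analysis section has "Both absolute values and percentage changes from baseline will be analyzed". Neither sentence names an outcome to which it does not apply. Satisfaction gets its own method, Fisher's exact test on a dichotomy. The exertion ratings get no separate treatment.

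On the ratings themselves, Outcomes says "Volunteers will complete two identical RPE scales ranging from 0 to 100, corresponding to muscular and cardiorespiratory effort". The schedule there reads "subjective perception of exertion (assessed at 1, 24, and 48 hours post-WOD", with no pre-WOD rating named. Study Sessions and Exercise Protocol says more generally "Assessments will occur before and after each WOD", and the Abstract also places an assessment of muscle recovery at baseline. On the state of participants at that baseline, the same section says they "will avoid physical activity from 24 h pre-WOD to 48 h post-WOD".

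No section gives a resting exertion value, a rule for a baseline of zero, or an order of precedence between the absolute and percentage results.

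**The concern.** Percentage change needs a denominator that is positive and not close to zero. Zero is a permitted score on these scales, and the baseline is taken in healthy, trained men after a day without exercise. A zero or low rating is plausible, most of all for RPE-R, which concerns cardiorespiratory fatigue.

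Where the baseline is zero, the observation has no percentage value and must be dropped or patched by a rule that the protocol does not give. Where it is low, a few small denominators govern the mean and the standard deviation. In a crossover the denominator also changes from session to session within the same person. A resting difference of a point or two, unrelated to the intervention, can then look like a large treatment contrast.

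The schedule adds a second difficulty. If the Outcomes list is complete, there is no pre-exercise rating to divide by.

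**Working it through.** The protocol gives no baseline rating, SD, effect size or sample size for exertion, so there is no planned figure to reproduce. The inputs from the protocol are the 0–100 range, the rating times, the 24-hour rest and the percentage rule. Every rating value below is an assumption.

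**Step 1: the measure at single values.** Percentage change = 100 × (post − baseline) / baseline. With a post-WOD rating of 30:

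- baseline 0: undefined
- baseline 1: 100 × 29/1 = +2900%
- baseline 2: 100 × 28/2 = +1400%
- baseline 5: 100 × 25/5 = +500%
- baseline 10: 100 × 20/10 = +200%
- baseline 20: 100 × 10/20 = +50%

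A baseline of 1 instead of 2 moves the result by 2900 − 1400 = 1500 percentage points.

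**Step 2: weight given to a treatment difference.** Suppose two interventions leave a participant at 40 and 30, with the same baseline in both sessions. The difference is 100 × 10 / baseline: 1000 percentage points at baseline 1, 200 at 5 and 50 at 20. The same 10-point benefit counts 1000/50 = 20 times as much in the participant who starts at 1 as in the one who starts at 20.

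**Step 3: effect on the comparison.** A simulation of 400,000 paired ratings assumed post-WOD means of 40 and 30, SD 12 and within-person correlation 0.5. Baselines were whole numbers cut off at 0, and pairs with a zero baseline were left out of the percentage analysis. The standardised effect is the mean paired difference divided by its SD.

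| Assumed baseline mean (SD) | Baselines equal to 0 | SD of paired % difference | Standardised effect, % scale | Standardised effect, points |
|---|---|---|---|---|
| 2 (2) | 23% | 1654 | 0.30 | 0.83 |
| 5 (4) | 13% | 1260 | 0.21 | 0.83 |
| 10 (6) | 6% | 859 | 0.17 | 0.84 |
| 20 (8) | 0.7% | 373 | 0.17 | 0.83 |
| 40 (10) | about 0% | 66 | 0.41 | 0.84 |

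Baselines were drawn independently of each other and of the post-WOD ratings. Correlated ratings would change the figures, so the table shows direction and rough scale only. Under these assumptions the percentage scale is much less sensitive than points at every baseline tried, including those where zeros almost vanish.

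**Step 4: the schedule.** There are two readings. If Outcomes lists every exertion rating, the denominator does not exist. If the Abstract and Study Sessions govern, the denominator exists and Steps 1 to 3 apply. The percentage rule is unsuitable on either reading.

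**The case against.** The strongest reply is that the harm is small. The same sentences that plan percentage change also plan absolute values, so exertion in points is already in the analysis. The primary outcome is jump performance at 1 hour, and the sample size uses percentage change in that measure. This stands, and it limits the point to one of two parallel analyses of a secondary outcome.

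A reader might infer that the resting rating is at or near zero. The documents do not show that. RPE-MI is lower-limb fatigue in men who train at least four times a week, and the trial itself rates exertion after 24 and 48 hours of enforced rest, so some residual fatigue at baseline is possible. At an assumed mean of 20, under 1% of baselines are zero.

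A reader might also infer that no pre-WOD rating is taken. That is not established either. Outcomes names only post-WOD times for the jump test too, and that outcome is a change and so must have a baseline. The general statements can be read as supplying a baseline for exertion as well. What remains is an ambiguity to be settled.

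Finally, the rule may not have been meant for every outcome, since it cannot apply to satisfaction, and the handling of zero denominators is often left to a statistical analysis plan. Both are fair. But satisfaction is given its own method and exertion is not. The choice of scale is also stated in the protocol twice; it is not a detail left open.

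**Conclusion.** The point holds in a limited form. As written, the percentage rule covers RPE-MI and RPE-R. It gives no value at a zero baseline and a very unstable one at a low baseline, and it cannot be computed if the Outcomes list is the whole schedule. How often zero or low baselines would occur is unknown, because the protocol gives no resting rating. The numerical illustrations rest entirely on assumed values.

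It would go too far to conclude that exertion will yield no usable result. The absolute analysis remains, and at moderate baselines the percentage can be computed, though it serves the scale poorly. The protocol also does not state that participants with a zero baseline would be removed from the whole analysis, so no figure for lost participants can be drawn from it.

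The correction is still worth making, because the protocol does not say which scale prevails if the two disagree. An unstable percentage result could then be reported with the same standing as the result in points.

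**What to change.** In the Abstract and in Statistical Analysis, limit percentage change from baseline to jump height and the biochemical markers. State that RPE-MI and RPE-R are analysed in points only, at 1, 24 and 48 hours, with adjustment for the pre-WOD rating if one is taken. That rating would differ by session, so the adjustment is most easily made in a linear mixed model.

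Reconcile Outcomes with the Abstract and with Study Sessions and Exercise Protocol, so that all three say the same about whether exertion is rated before the WOD.

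The cost is about a sentence of analysis text and a few words in the schedule. Neither the sample size nor the primary analysis changes.

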**BACKGROUND**

Cross Training emerged in the early 2000s as a method of strength and conditioning training (Meyer et al., 2017). Training is based on the combination of functional movements, constantly varied and performed at high intensity, called WOD (Workout of the Day) (Butcher et al., 2015). A WOD consists of a wide range of movements, such as weightlifting exercises (deadlift, bench press, squats), Olympic lifts (snatch and clean and jerk), gymnastics and calisthenics exercises, such as pull-ups, push-ups, sit-ups, and burpees (Butcher et al., 2015; Drum et al., 2017). In addition, Cross Training includes cardiorespiratory stimuli such as running, cycling, rowing, jumping rope, and other plyometric activities (Drum et al., 2017). These stimuli are often combined and performed at high intensity, with fast, successive repetitions and with little or no recovery time (Tibana et al., 2016).

WODs are scored and often involve competitive elements among participants, a feature that has led this method of functional exercise to be recognized as the “Sport of Fitness” (Hak et al., 2013). The official Cross Training competition, known as the CrossFit® Games, was first held in 2007 with 70 athletes, and in recent years participation has expanded to more than 324,000 athletes worldwide (https://games.crossfit.com/history-of-the-games). In this competition, winners are recognized as the best-conditioned athletes in the world, “The Fittest on Earth” (Dawson, 2015).

According to Claudino et al. (2018), Cross Training is considered an excellent option of HIIT (High-Intensity Interval Training). HIIT is a type of interval training at high intensity that improves both anaerobic and aerobic energy supply systems (Tabata et al., 1996; Zhang et al., 2017). When applied to different sports and in Cross Training competitions, HIIT effectively overloads both anaerobic and aerobic energy systems, resulting in improved athletic performance (Tabata et al., 1997; Jagim et al., 2015). However, Cross Training as a sport differs from HIIT by including gymnastic and weightlifting elements, and by reducing or eliminating rest periods (Meyer et al., 2017; Kliszczewicz et al., 2015). As observed in traditional competitions, the main goal of WODs is to complete a specific number of repetitions and exercises in the shortest possible time (Kliszczewicz et al., 2015). Thus, since athletes are often subjected to several WODs on the same day and on consecutive days of competition, they must cope with fatigue and the resulting muscle recovery demands (Hak et al., 2013).

This high physical demand required in intense exercise has raised concerns in the scientific community, as confirmed by several publications investigating the relationship between Cross Training practice and the risk of injuries (Hak et al., 2013; Weisenthal et al., 2014; Sprey et al., 2016; Summitt et al., 2016; Maté-Muñoz et al., 2017). Weisenthal et al. (2014) concluded that fatigue causes alterations in movement biomechanics, increasing injury risk. According to Hak et al. (2013), in their analysis of the nature and prevalence of injuries in Cross Training practitioners, the loss of technique during extreme fatigue is associated with lumbar spine injuries. Maté-Muñoz et al. (2017) added that many exercises used in Cross Training require advanced technique as well as high sustained power output. Therefore, they can induce considerable fatigue and lead to injuries in subsequent training sessions. The fatigue process leads to a decline in physical performance and, in some cases, to injuries (Andersson et al., 2008; Ispirlidis et al., 2008; Nédélec et al., 2012). Thus, it can be inferred that the risk of injury is closely related to fatigue generated by the high intensity required during WOD performance (Hak et al., 2013; Weisenthal et al., 2014; Maté-Muñoz et al., 2017).

The development of muscle fatigue is a complex and multifactorial process that may be associated with muscle oxidative stress caused by increased production of reactive oxygen species (ROS) after strenuous exercise (Reid et al., 1992; Vollaard et al., 2005; Reid et al., 2016). To investigate fatigue during two consecutive Cross Training sessions, Tibana et al. (2016) analyzed physiological responses of blood markers such as creatine kinase (CK), interleukins 6 and 10 (IL-6, IL-10), osteoprotegerin, lactate, and glucose. Based on their results, the authors highlighted the importance of lower-intensity sessions and/or rest days to help minimize immune disturbances and possible causes of fatigue (Tibana et al., 2016). Similarly, Heavens et al. (2014) analyzed the effects of high-intensity training on CK, IL-6, myoglobin, and testosterone markers and concluded that training intensity should be individually scaled to minimize injury risk. They also pointed out the importance of recovery periods and rest days between high-intensity training sessions (Heavens et al., 2014). Some studies assessing blood markers after strenuous exercise suggest that the increase of these cytokines is associated with muscle damage and elevated neutrophil count during muscle recovery (Yamada et al., 1985; Bruunsgaard et al., 1997).

Muscle recovery strategies involve the implementation of a single or combined technique to enhance and accelerate recovery after exercise, better preparing the athlete for the next activity and reducing the risk of injury (Dupont et al., 2010; Pinto et al., 2016). Sports-related studies have sought tools to minimize exercise-induced damage, optimize training intervals, increase performance, and prevent injuries (Kellmann et al., 2010). According to Kellmann et al. (2010), the difference between success and failure in modern sports is directly related to recovery effectiveness. Supporting this claim, Feito et al. (2018) indicated that rapid and efficient muscle recovery capacity is an important factor for better performance in Cross Training. Therefore, there is evidence highlighting the relevance of investigating resources that promote muscle recovery according to the physical demands of the sport. Historically and clinically, several therapeutic resources have been employed to recover from muscle fatigue and, consequently, enhance performance in athletes, regardless of the strength of scientific evidence, and they are widely applied in clinical practice (Altarriba-Bartes et al., 2020).

Some therapeutic modalities are commonly used for muscle recovery in sports practice, such as massage (Hoffman et al., 2016), cryotherapy (Micheletti et al., 2019), intermittent pneumatic compression – IPC (Hoffman et al., 2016), extracorporeal shock wave therapy – ESWT (Fleckenstein et al., 2017), and photobiomodulation therapy – PBMT (Tomazoni et al., 2019; De Marchi et al., 2019). Recent studies have evaluated IPC, ESWT, and PBMT, and have suggested positive outcomes (Hoffman et al., 2016; Tomazoni et al., 2019; De Marchi et al., 2019).

IPC, used both by athletes and in rehabilitation clinics, consists of inflatable chambers/boots that surround the limb and sequentially inflate with air to apply pressure (Hoffman et al., 2016; Martin et al., 2015; Haun et al., 2017; Overmayer et al., 2018). Studies suggest that negative pressure can improve recovery and reduce muscle soreness after strenuous exercise (Hoffman et al., 2016; Martin et al., 2015). IPC works by improving venous return at a circulatory level, theoretically enhancing muscle blood flow, increasing tissue oxygenation, and positively influencing muscle recovery (Zuj et al., 2019). Furthermore, IPC has shown satisfactory results in various vascular dysfunctions such as lymphedema, severe chronic venous insufficiency, peripheral arterial occlusive disease, and thrombosis prophylaxis (Schwahn et al., 2018). However, some studies report inconclusive results regarding IPC for reducing fatigue and improving muscle performance, which may be related to the lack of standardized parameters for this purpose, since parameters used vary widely (Hoffman et al., 2016; Cochrane et al., 2013; Martin et al., 2015; Overmayer & Driller, 2017).

With effective results in systematic reviews for a variety of musculoskeletal clinical conditions, ESWT has been emerging as a potential new treatment option (Schmitz et al., 2015; Alabbad et al., 2020). ESWT delivers three-dimensional pressure pulses concentrated in microseconds with peak pressures of 35–120 MPa, applied to small focal areas of 2–8 mm in diameter, perpendicularly to the tissue (Alabbad et al., 2020). Its mechanisms of action include effects on tissue calcifications, alterations in cellular activity through cavitation, acoustic microstreaming, changes in cell membrane permeability, and effects on nociceptors through hyperstimulation, blocking the pain gate-control mechanism (Speed et al., 2014). Satisfactory effects have been found in stimulating skeletal muscle tissue regeneration and accelerating repair processes in acute muscle injury, indicating increased proliferation and differentiation rates of satellite cells (Zissler et al., 2017). Moreover, ESWT has demonstrated positive results in clinical studies for injury rehabilitation, muscle recovery in athletes (Speed et al., 2014; Fleckenstein et al., 2017), and reduction of muscle soreness (Fleckenstein et al., 2017; Notarnicola et al., 2018; Taheri et al., 2016; Jeon et al., 2012). Fleckenstein et al. (2017) examined the effects of a single ESWT application on delayed onset muscle soreness induced by eccentric exercise and observed clinically relevant effects in pain relief and increased muscle strength. Similarly, Notarnicola et al. (2018) demonstrated significant increases in muscle elasticity, tone, and fiber recruitment with ESWT applied to the quadriceps. ESWT has also shown positive outcomes in musculoskeletal dysfunctions such as epicondylitis, subacromial pain syndrome, plantar fasciitis, and tendinopathies (Schmitz et al., 2015). These results point to ESWT as a possible tool to help delay fatigue and improve muscle performance, although few studies have demonstrated its effects on muscle recovery after strenuous exercise in athletes.

Recent studies on PBMT have shown satisfactory results for both reducing fatigue markers and enhancing performance and muscle strength (Tomazoni et al., 2019; De Marchi et al., 2019; Pinto et al., 2016; Vanin et al., 2018; Leal-Junior et al., 2019; Baroni et al., 2010; Antonialli et al., 2014; De Paiva et al., 2016; Vanin et al., 2016). Results suggest attenuation of delayed-onset muscle soreness and smaller increases in blood markers of muscle damage when PBMT is used compared to control groups (Baroni et al., 2010; De Paiva et al., 2016). Its mechanism of action is related to enhanced electron transfer, consequently activating mitochondrial respiratory chains and increasing mitochondrial adenosine triphosphate (ATP) production (Miranda et al., 2018; Wang et al., 2018). Tomazoni et al. (2019) showed that pre-exercise PBMT, as a standalone therapy, was able to improve different functional aspects related to athletic performance and biochemical markers of muscle damage and inflammation in elite athletes. Additionally, PBMT demonstrated antioxidant effects, reducing exercise-induced oxidative stress and promoting ergogenic and protective effects on skeletal muscles (Tomazoni et al., 2019).

Furthermore, studies have reported positive outcomes using PBMT combined with a static magnetic field – PBMT-sMF (Antonialli et al., 2014; De Paiva et al., 2016). The magnetic field enhances ATP production and helps reduce oxidative stress, thereby potentiating the effects of PBMT (Friedmann et al., 2019; Wang et al., 2018; Coballase-Urrutia et al., 2018). According to Pinto et al. (2016), in a field test with rugby athletes, PBMT-sMF improved performance and promoted faster muscle recovery.

However, evidence on the effectiveness of some of these recovery strategies remains conflicting (Brown et al., 2017; Poppendieck et al., 2016). Considering the high-intensity effort required in Cross Training, the use of resources that support the muscle recovery process is of great value, as it can ensure athletes are fit to perform subsequent WODs with reduced injury risk. Thus, advancing the development and understanding of therapies or resources tailored to the recovery needs of Cross Training athletes is highly important for optimal performance in this sport. The present study seeks to compare therapeutic resources frequently employed in clinical practice in order to determine the most suitable for muscle recovery associated with Cross Training practice.

